##### Data collection tools and techniques

Ten data collectors will be recruited and trained for 2 days. A structured questionnaire prepared in Afan Oromo will be used to collect data. Components in the questionnaire will be prepared by adapting tools validated for use in similar contexts. Data will be collected at baseline, 1st month and 6th month. Data collection interviews will be made 1–3 days before counselling visits. Data on socioeconomic and demographic variables, maternal and pregnancy factors, and previous infant feeding experience will be collected at baseline. Information on delivery, about early initiation, whether colostrum was discarded, use of prelacteals, and reasons for delaying or not initiating breastfeeding will be obtained one month after birth. Data on knowledge and attitude will be collected at baseline and at study completion. Anthropometric measurements (length, weight and mid upper arm circumference (MUAC)) will be done at 6 month. Length will be measured using length board at a precision of 0.1 cm. Infant’s weight will be measured to the nearest 1.0 g using UNICEF SECA weighing scales with light clothing. MUAC will be measured to the nearest 0.1 cm on the left arm using non- stretchable MUAC tape. Length and MUAC measurements will be done in duplicate. The measurement procedures will follow standard WHO guidelines [54]. All data collectors will be trained on content, questionnaire techniques and measurements and will be kept uninformed about cluster allocation. Reproducibility and validity exercises will be conducted for the weight and length measurements. Mothers’ and WDA leaders’ experience about the intervention will be assessed qualitatively at study completion. To obtain feedback on the intervention, individual semi-structured interviews will be held with intervention mothers at the end of 6 months after end-line data is collected. Additionally, focus group discussions will be carried out with WDA leaders to assess their opinions about the intervention strategy. All group discussions will be moderated by the principal investigator. Another person will take notes while the discussions are simultaneously audio-taped. Additionally, a field memo will be completed for each FGD and interview, and socio- demographic data will be collected for all participants based on a brief questionnaire (e.g., age, education, etc.). The memos will include observations about the group dynamics, information about non-verbal responses, questions that elicited hesitations or any interruptions or difficulties in running the focus groups. Breastfeeding Knowledge and Attitude (B-KA) questionnaire will be developed and adapted using the following validated instruments: the Iowa Infant Feeding Attitude Scale (IIFAS) [55] and the Breastfeeding Knowledge Questionnaire (BKQ) [56].

##### The Iowa infant feeding attitudes scale (IIFAS)

The Iowa Infant Feeding Attitudes Scale (IIFAS) was developed in 1999 by de la Mora [55]. The scale was designed to assess maternal attitude toward infant feeding methods and to predict breastfeeding intention and exclusivity. It is composed of 17 items with a 5-point Likert scale ranging from 1 (strongly disagree) to 5 (strongly agree). Eight items are worded in manner favoring breastfeeding, whereas the other 9 favors bottle feeding. Items favoring bottle-feeding are reverse scored. The total IIFAS score ranges from 17 (reflecting positive attitudes toward bottle-feeding) to 85 (reflecting more positive attitudes toward breastfeeding). It has been validated in different countries such as the United States [55], Northern Ireland [57], Scotland [58], Japan [59], Romania [60] and China [61].

##### Breastfeeding knowledge questionnaire

The questionnaire assessing breastfeeding knowledge was adapted and modified from a breastfeeding questionnaire developed by a team of pediatric nurses at the Hospital Universiti Sains Malaysia (HUSM) [58]. Items in the modified questionnaire covered the following scopes of knowledge on breastfeeding: general knowledge, colostrum, advantages to mothers and babies, effective feeding method, duration of feeding, expressed breast milk (EBM), storage of EBM, complementary feeding, and problems with breastfeeding.

##### Instrument translation

Permission to use both instruments will be obtained from authors. A systematic process recommended by Beaton et al. [62] will be used for maintaining semantic, idiomatic, experiential and conceptual equivalence. The instruments will be forward translated to Afan Oromo by bilingual translators. Two bilingual translators who are totally blind to the original English version will translate the instruments back to English. The back-translation is essential to establish semantic equivalence. An expert committee meeting will be held to consolidate all versions of translation to develop the pre-final version of the questionnaire for field testing.

The original and the back-translated English version of instruments will be compared to check for the accuracy of translation. A method developed by Skperber et al. [63] will be used for validating the translated instrument where each item in the original and back-translated versions will be ranked in terms of comparability of language and similarity of interpretability. Ranking will be done by raters who are fluent in English using Likert scales ranging from1 (extremely comparable/extremely similar) to 7 (not at all comparable/not at all similar). Any mean score > 3 requires a formal review of the translation. The translated instruments will then be piloted among 30 pregnant women to assess its clarity, comprehension, length, and cultural acceptability. The questionnaires will finally be used to assess knowledge and attitude of study participants who will be enrolled into the trial at baseline and completion of the study.

##### Data management

All filled questionnaire will be checked for completeness by supervisors and questionnaires with missing items will be returned to data collectors for correction. Participants who are lost to follow up will be recorded along with their reasons. The following standard processes will be implemented to improve the accuracy of data entry and coding: double data entry; verification that the data are in the proper format (eg, integer) or within an expected range of values; and independent source document verification of a random subset of data to identify missing or apparently erroneous values. Only the study team will have access to the trial datasets. In order to ensure confidentiality, information about each zone and personal data of participants will not be shared with any third party both during and after the trial. Additionally, all personal identifiers will be removed from database and filled questionnaires will be stored in a locked cabinet. Data will be stored in a database on a password protected computer and only accessible by the study team.

##### Data processing and analysis

Double data entry will be performed using EpiData version 3.1 (EpiData Association) and consistency checks and statistical analysis will be done using Stata version 13.1 (StataCorp). The effect of the intervention in comparison with the routine education will be assessed by fitting mixed-effects linear regression models for the continuous outcomes and mixed-effects linear probability models for the binary outcomes using study zone as random intercept to account for clustering of subjects by zones. The use of linear probability model for binary outcomes is well-established and allows for a straightforward interpretation of the average intervention effect expressed as risk difference using percentage points [64]. Fixed-effects in the models will include study arm (intervention vs. routine education), baseline value of the outcome when appropriate, and additional covariates that could potentially confound estimation of group difference. Potential covariates will be selected based on consideration of study arm balance at baseline and potential confounders for an outcome previously reported in the literature. Potential confounders of timely breastfeeding initiation include: place of delivery, mode of delivery [65] whereas potential confounders of EBF are mode of delivery, age, parity, educational status, previous BF experience, household income and breastfeeding intention [30, 65–68]. We will further explore effect modification of the intervention by the different covariates by adding interaction terms between study group and a covariate as fixed-effect parameter. Subgroup analysis of the intervention effect by a covariate will be considered when there is significant interaction (*P* < 0.1) between the intervention and a covariate. Moreover, mean values of anthropometric data of infants in the intervention and control groups will be compared using Student’s t test and linear regression will be used. In all analyses, adjustment will be made for clustering at the zone level since randomization was done at cluster level rather than individual level.

All analyses will be performed by the intention-to-treat principle including all subjects initially enrolled into the study. For this purpose, we will conduct a multiple imputations procedure for the missing data using chained equations under the missing at random assumption. Fifty imputations of missing data will be generated to estimate the regression coefficients. All tests will be two-sided and the level of significance will be set at alpha < 0.05. No interim analyses are planned and all outcomes will be analyzed after data collection is completed.

All FGDs and interview audio files and notes will be translated to English, then transcribed verbatim and analyzed thematically using Systematic Text Condensation, a descriptive and explorative analysis strategy in Atlas Ti7 software. Malterud’s text condensation follows four steps: 1) total impression - from chaos to themes; 2) identifying and sorting meaning units - from themes to codes; 3) condensation - from code to meaning; 4) synthesizing - from condensation to descriptions and concepts. It is a qualitative research method particularly suited to analyze qualitative data, such as interview studies, observational studies and the analysis of written texts [69].

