#### Recruitment

Before cluster randomization, all pregnant women in the randomized zones will be identified by reviewing Health Extension Worker’s logbook. However, recruitment will be started after clusters have been randomized. During recruitment, WDA leaders will additionally be used to identify pregnant women in their 1–5 network to minimize the chance of missing any pregnant women in each cluster zone. Identified pregnant women will be invited to a meeting at the health post where the nature and purpose of the trial and eligibility criteria will be explained.

Informed consent will be obtained from each woman prior to their inclusion in the trial. Verbal consent will be obtained to ensure approval by the woman that she could be visited by WDA leaders for the intervention. Then the written consent will be obtained from all women who will be enrolled into the study. The data collectors will explain all trial procedures from inclusion criteria to the last follow-up using an information sheet. The women will be allowed to ask questions and relevant information will be provided accordingly. The data collectors will be trained using simulation situations. Women who are willing to consent will either sign or put their finger-prints according to their literacy status. If a woman declines, a form will be filled and she will be thanked. All women in the intervention clusters will receive the breastfeeding education and support if they wish to do so, whether they participate in data collection or not. To retain study participants with complete follow up there will be repeated visits. Unless a clear reason for non-participation at a scheduled visit is given, three attempts to visit the mother-infant pair will be made before a visit is considered as missed. A recruited mother will be revisited until the last scheduled visit, irrespective of the number of missed visits, unless there is a clear reason for termination. Regardless of decision to discontinue their assigned intervention, study participants will be retained in the trial whenever possible to enable follow up data collection and prevent missing data. All pregnant women in the randomized clusters will be identified and approached in order to minimize selection bias. Participants are enrolled from May to August 2017.

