##### Intervention group

Women in the intervention group will receive an enhanced breastfeeding education and support intervention from third trimester during pregnancy till 5 months post-delivery. The intervention is composed of the following elements: a) prenatal breastfeeding education to raise knowledge and awareness where benefits of breastfeeding will be emphasized, b) postnatal breastfeeding counselling and support.

After being trained, WDA leaders will provide breastfeeding education and support through a house to house visit before and after delivery. Besides the routine information and education HEWs and WDA leaders provide to the women, each visit will be designated to cover specific topics related to the outcomes of the study.

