##### Education and support by peer-supporters during pregnancy

WDA leaders will function as peers for mothers in their clusters. During each visit WDA leaders will, in addition to a specific topic from the health package, cover in detail the importance of timely initiation of breastfeeding and EBF, feeding colostrum first, and discouraging prelacteal and postlacteal foods and encourage the mother to deliver at the nearby health center. The discussion will be combined with use of educational materials and practical demonstrations on proper breastfeeding positioning and attachment. Mothers will be encouraged to ask any question related to topics discussed.

WDA leaders will use language and culturally appropriate visual educational materials in the form of flip charts to illustrate the new information (e.g., correct and incorrect breastfeeding positions, correct and incorrect breastfeeding latching on, examples of how the father/significant others can support the mother with breastfeeding), and the benefits of applying this new information to practice (e.g., pictures of babies who were breastfed versus those who were not).

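### Place and mode of delivery are named as adjustment covariates, but both arise after randomisation, and place of delivery is a possible mediator of the effect on timely initiation

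*Protocol article*

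**What the plan says.** The section on data processing and analysis specifies mixed-effects linear probability models for the binary outcomes, with zone as random intercept and the effect expressed as a risk difference. The fixed effects are study arm, the baseline value of the outcome where appropriate, and "additional covariates that could potentially confound estimation of group difference". The Abstract likewise describes the arm difference as covariate-adjusted.

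Two routes lead into the model. One is balance: "Potential covariates will be selected based on consideration of study arm balance at baseline". The other is confounders reported in the literature. Under the second route the text gives outcome-specific lists:

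- Timely initiation: "Potential confounders of timely breastfeeding initiation include: place of delivery, mode of delivery". No other variable is named.
- EBF: "potential confounders of EBF are mode of delivery, age, parity, educational status", followed by previous breastfeeding experience, household income and breastfeeding intention.

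The same paragraph plans interaction terms between arm and the covariates, with subgroup analysis where the interaction has P < 0.1.

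Timely initiation and EBF at 6 months are both primary outcomes (Outcome assessment). The primary objective is superiority of the intervention over usual care, and all analyses are to follow the intention-to-treat principle.

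**The concern.** A confounder of a randomised comparison has to be in place before allocation can act. Place and mode of delivery are not. Place of delivery is, in addition, something the prenatal education tries to influence. Holding it constant means comparing arms among women who delivered in the same kind of place, which leaves out any benefit that arises because more women delivered at a facility.

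What is at stake is the meaning of the estimate for a primary outcome. The stated objective, the intention-to-treat principle and the scale-up decision described in the Discussion all call for the total effect of the intervention. A model with place of delivery as a fixed effect estimates something closer to a direct effect. If place of delivery and early initiation also share unmeasured causes, it does not estimate even that cleanly. The most likely direction is toward no effect.

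**Working it through.** The article gives no figure for this model, and its sample size calculation concerns EBF only, so there is no stated number to reproduce. The check has two parts.

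**1. Timing and content**

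| Point | Text | Section |
|---|---|---|
| Zones are allocated before women enter | "recruitment will be started after clusters have been randomized" | Recruitment |
| Intervention starts before delivery | "from third trimester during pregnancy till 5 months post-delivery" | Intervention group |
| Prenatal message on place of delivery | "encourage the mother to deliver at the nearby health center" | Education and support by peer-supporters during pregnancy |
| Delivery data come one month after birth | "Information on delivery, about early initiation, whether colostrum was discarded" | Data collection tools and techniques |

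Every delivery therefore follows randomisation, and delivery variables are recorded at the month-1 contact, not at baseline. They cannot be chosen for baseline imbalance; they enter only through the literature route. Place of delivery is an explicit target of the prenatal visits. Nothing in the article makes mode of delivery a target; it could be affected only indirectly, for example through place.

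**2. How much could be removed**

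Let dF be the intervention's effect on facility delivery and g the effect of facility delivery on timely initiation. Neither is in the article; both are assumptions here. In a linear probability model with arm and facility delivery:

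- total effect = direct effect + dF × g
- effect adjusted for facility delivery = direct effect, if place and initiation share no other cause
- amount removed = dF × g

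Amount removed, in percentage points:

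| dF | g = 10 | g = 20 | g = 30 |
|---|---|---|---|
| 0 | 0 | 0 | 0 |
| 5 | 0.5 | 1.0 | 1.5 |
| 10 | 1.0 | 2.0 | 3.0 |
| 20 | 2.0 | 4.0 | 6.0 |

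A simulation with an assumed direct effect of 10 points agrees:

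- dF 5, g 10: total 10.57, adjusted 10.06
- dF 10, g 20: total 12.02, adjusted 10.05
- dF 20, g 30: total 16.04, adjusted 10.05

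**With a shared cause.** Suppose a factor present in half of the women raises facility delivery by 30 points and initiation by 15 points, with facility delivery averaging 40% in the control arm and 60% in the intervention arm (dF 20, g 20).

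- Covariance induced within arm: 0.30 × 0.15 × 0.25 = 0.01125
- Variance of facility delivery within arm: 0.4 × 0.6 = 0.24
- Coefficient of facility delivery: 0.20 + 0.01125 / 0.24 = 0.247
- Amount removed: 0.20 × 0.247 = 0.049

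The total effect of 14.0 points becomes about 9.1, below the direct effect of 10. The simulation gave 14.05 and 9.10. With a shared cause some distortion can remain even if g is zero. If dF is zero, nothing is removed in either setting.

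**The case against.** Several points can fairly be put on the other side.

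- **The covariates are only candidates.** The text calls them potential and says they will be selected. That stands, so it cannot be said that the final model will contain them. But for timely initiation the article names these two and no others, so the only outcome-specific guidance it gives points to post-randomisation variables.
- **The contrast in place of delivery may be small.** Routine care already has health extension workers accompany women to a facility (Control group). This may reduce dF, possibly to near zero. It does not turn place of delivery into a baseline variable.
- **Adjustment has a legitimate purpose here.** Women are recruited after zones are allocated, so the arms may differ through identification or consent and not by chance alone. That stands, and it supports adjusting for pregnancy-baseline variables. It does not support adjusting for something that happens later and that the intervention promotes.

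Some stronger readings are tempting but not supported:

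- A reader might infer that the intervention tries to change mode of delivery as well. No section says so; the objection to mode of delivery is one of timing only.
- A reader might infer that selecting covariates on observed balance is itself an error because any imbalance is chance. That does not fit a cluster trial which recruits after allocation, and the final covariate list is commonly left to the analysis plan.
- A reader might infer that the analysts can tune the model because month-1 data exist. Trial status says only that those data were collected, and all outcomes are to be analysed after data collection is completed.
- A reader might translate the lost points into lost power from a 73% control rate. The 73% is a national survey figure in the Background, not a planning assumption for this trial.

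**Conclusion.** The point holds as a conditional one. The article names place and mode of delivery as confounders for a primary outcome although both follow randomisation and the start of the prenatal visits. Place of delivery is a possible mediator; mode of delivery is only a post-randomisation variable, here and in the EBF list. Adjusting for place departs from the total intention-to-treat effect if two things hold: the intervention shifts where women deliver, and place affects initiation.

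The article quantifies neither. Under assumed shifts of 5 to 20 points and facility effects of 10 to 30 points, 0.5 to 6 percentage points of risk difference are removed. None is removed if there is no shift, or if place has no effect and shares no cause with initiation. A shared cause can make the loss somewhat larger. A reader might infer that the estimate is certainly biased; the article does not support that, because the size may be zero. The covariate choice is nevertheless wrong as written, since no value of these quantities makes either variable a baseline confounder.

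**What to change.** In the section on data processing and analysis:

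1. Remove place and mode of delivery from the main effect model for timely initiation, and mode of delivery from the main effect model for EBF.
2. Exclude both from the interaction and subgroup analyses, since subgroups defined by them would be formed after randomisation.
3. State that the main models adjust only for variables measured at the pregnancy baseline. Examples already named for EBF are age, parity, education and previous breastfeeding experience. Household income and breastfeeding intention qualify if they were recorded at baseline; the data collection section does not list them explicitly.
4. If place or mode of delivery is of interest, report any model containing it separately, labelled as exploratory or as a mediation analysis.

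The cost is a change of wording. No new data are needed, and because all outcomes are to be analysed after data collection is completed, the change can be recorded before analysis begins.

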##### Outcome assessment

**Primary outcomes** of the trial include timely initiation of breastfeeding, exclusive breastfeeding at 6 month and infant growth**.**

**Timely breastfeeding initiation** is measured as the proportion of women who initiated breastfeeding her baby within the first hour after delivery.

**Exclusive breastfeeding at 6 month** is measured as the proportion of women who provided their infants with only breast milk but no solids, nonhuman milk, water, or other liquids (other than vitamins or medications) at six months.

**Infant growth** - WHO Child Growth Standards (2006) will be used to estimate anthropometric status at 6 month [53]: weight-for length z-scores (WLZ), length-for-age z-scores (LAZ) and weight- for-age z-scores (WAZ). Children who have WLZ below− 2 (WLZ < − 2) will be considered wasted, those with LAZ below− 2 (LAZ < − 2) stunted, and those with WAZ below − 2 (WAZ < − 2) underweight.

**Secondary outcomes are** validation of the Afan Oromo version breastfeeding knowledge and attitude questionnaire, baseline knowledge, attitude and practice of mothers on breastfeeding, change in mothers’ knowledge and attitude towards breastfeeding at baseline and study completion, mothers' and WDA leaders' experiences of the intervention at study completion.

Outcomes will be assessed as illustrated in the Standard Protocol Items: Recommendations for interventional trials (SPIRIT) (Table 1).

**Table 1 Tab1:** Standard Protocol Items: Recommendations for Interventional Trials (SPIRIT)

Outcomes	Allocation	Study period			
		Enrollment		Close-out	
	-t_1_	Baseline (t_0_)	Intervention (8 months)	Midline at month 1 after delivery (t_1_)	End line at month 6 (t_2_)
Enrollment					
Allocation	x				
Eligibility screen		x			
Informed consent		x			
Interventions					
BFES Intervention			x		
Control group			x		
Assessments					
Background/demographics		x			
Water, Hygiene and Sanitation		x			
Household Food Insecurity Access Scale		x			
Food Taboos during Pregnancy & Lactation		x			
Mother’s Health Status & Obstetric history		x			
Current pregnancy and breastfeeding		x			
Timely breastfeeding initiation				x	
Exclusive breastfeeding at 6 month					x
Infant growth					x
Validation of the Afan Oromo version breastfeeding knowledge and attitude questionnaire			x		
Baseline knowledge, attitude and practice of mothers on breastfeeding			x		
Change in mothers’ knowledge and attitude towards breastfeeding at baseline and study completion			x		x

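### Exploratory subgroups are selected by an unadjusted interaction P < 0.1 over an open covariate list that includes delivery factors arising after randomisation

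*Protocol article*

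**What the plan says.** All of this is in the protocol article, mainly under Data processing and analysis.

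- The search for effect modification: "We will further explore effect modification of the intervention by the different covariates by adding interaction terms between study group and a covariate".
- The gate: "Subgroup analysis of the intervention effect by a covariate will be considered when there is significant interaction (*P* < 0.1) between the intervention and a" […].
- The covariates for initiation: "Potential confounders of timely breastfeeding initiation include: place of delivery, mode of delivery".
- The covariates for EBF: "potential confounders of EBF are mode of delivery, age, parity, educational status, previous BF experience, household income and breastfeeding intention".
- How the list is settled: "Potential covariates will be selected based on consideration of study arm balance at baseline and potential confounders for an outcome previously reported in the literature". The number of interaction tests is therefore not fixed.
- The general level: "All tests will be two-sided and the level of significance will be set at alpha < 0.05". No adjustment is stated for the interaction tests.

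Under Outcome assessment, the primary outcomes "of the trial include timely initiation of breastfeeding, exclusive breastfeeding at 6 month and infant growth". No covariates are named for growth.

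Two other sections bear on the point. Education and support by peer-supporters during pregnancy has the Women Development Army leaders urge women to give birth at a nearby health center. Data collection tools and techniques places the collection of delivery information one month after birth.

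**The concern.** The article states a selection rule: which subgroup effects are looked at depends on which interactions happen to pass P < 0.1. Three consequences follow.

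1. With several tests at 10% each, one or more is likely to pass by chance even if the intervention works equally well in all women.
2. In a trial of this size an interaction passes only if the observed difference between subgroups is large. What is shown because it passed is then biased upwards, and a modifier that did not pass is no evidence of a uniform effect.
3. Place and mode of delivery are not baseline characteristics. The intervention may change where a woman delivers, so the women delivering at a health center in the two arms need not be comparable. An effect within that subgroup is not a randomised comparison.

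At stake is how far any secondary statement about who benefits can be relied on. The overall effect estimates are not touched.

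**Working it through.** **The plan's own figure.** Inputs from Sample size determination: EBF 58% versus 78%, 80% power, two-sided 5%, ICC 0.1, 10 women per cluster.
- Two-proportion formula with continuity correction: 94 per arm.
- Design effect: 1 + (10 − 1) × 0.1 = 1.9.
- 94 × 1.9 = 178.6 per arm, 357.2 in total, or 35.7 clusters of 10, rounded to 36.
- 36 × 10 = 360, and 360 × 1.2 = 432.

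The stated 36 clusters and 432 women are reproduced. I use 360 analysed women, 180 per arm, below.

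**Number of tests.** Two covariates for initiation plus seven for EBF give nine outcome-covariate pairs. Mode of delivery is in both lists, so there are eight distinct covariates.

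**Chance that at least one passes when there is no effect modification.** Independent tests: 1 − 0.9^k.
- k = 7 (EBF alone): 52.2%
- k = 8: 57.0%
- k = 9: 61.3%; expected number passing 9 × 0.1 = 0.9

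For nine test statistics with a common correlation (assumed; the article gives none), simulation gives:

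| Correlation | At least one passes |
|---|---|
| 0.1 | 60% |
| 0.2 | 58% |
| 0.3 | 55% |
| 0.5 | 46% |

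**Size needed to pass, for EBF.** Assumptions: a binary covariate split 50:50 within zones (90 women per arm and level), EBF 58% in every cell, and within-zone variance p(1 − p)(1 − ICC).
- SE of the interaction = √[2 × 0.58 × 0.42 × 0.9 × (1/90 + 1/90)] = 0.0987, or 9.9 points.
- Smallest observed difference that passes: 1.645 × 0.0987 = 0.162, about 16 points.
- Mean absolute difference given a false pass: 2.06 × 0.0987 = 0.203, about 20 points. That equals the whole 20-point effect the trial is sized for.
- Power at two-sided 0.10: 27% for a true 10-point interaction (missed 73%) and 45% for a true 15-point one (missed 55%).

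With 78% EBF in the intervention arm the picture is similar: SE = √[0.9 × (0.58 × 0.42 + 0.78 × 0.22) × (2/90)] = 0.091, threshold about 15 points, power about 30% and 50%.

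**Effect of a Bonferroni criterion.** 0.1/9 = 0.011 per test holds the chance of any false pass at 1 − (1 − 0.1/9)^9 = 9.6%. The critical value rises to about 2.54, and power at SE 0.0987 falls to about 6% (10 points) and 15% (15 points).

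**Timing of the modifiers.** Women are enrolled while pregnant, after the zones are randomised. Place and mode of delivery are settled later, and place of delivery is something the prenatal visits try to influence. Parity, education and previous infant feeding are fixed before the first visit.

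**The case against.** The case for leaving the text alone has real force. The article speaks of exploring effect modification, and a subgroup analysis is only to be considered after a signal. Requiring an interaction test first is better practice than comparing P-values within subgroups, and a liberal level is a usual answer to low power. The general 0.05 level suggests that 0.1 is a screen and not a standard for claims. A modifier list and a multiplicity rule may also sit in an analysis plan that is not shown.

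Most of this stands, and it rules out several stronger readings that a reader might infer:
- *That the rule produces spurious subgroup claims in most trials.* The 57% to 61% is the chance of at least one flag. A flag is not a claim, and the article promises none.
- *That nine tests is a minimum.* The lists are of potential covariates from which some will be selected, so the number could be lower or higher. With strongly correlated tests the chance falls below one half.
- *That the growth scores push the chance close to certainty.* No covariates are named for growth.
- *That scale-up would be misdirected.* The Discussion ties scale-up to the overall effect on initiation and EBF.
- *That a multiplicity correction is required.* It would cut already low power to about 6% and 15%. That is a trade-off between two errors, and the present text is not wrong for lacking it.

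What the objection does not answer is the selection itself. Calling an analysis exploratory does not remove the exaggeration in effects shown because they passed a P-value. Nor does it make place of delivery a baseline factor. Both follow from what the article states, not from what it leaves out.

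**Conclusion.** The point holds as a weakness in a stated exploratory rule. It is not an error in the primary analysis. The gate performs poorly in both directions: it is likely to flag something by chance, and it misses most moderate interactions. The false-flag figures rest on nine pairs or eight covariates being tested, and on independence or an assumed correlation. The 16-point threshold and the power figures rest on an assumed 50:50 binary covariate with EBF at 58%. A less even split would raise the threshold, and age and income are not naturally binary. The timing problem needs no such assumptions. Both initiation covariates arise after randomisation, and for place of delivery the article itself describes a route by which the intervention could change it.

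**What to change.** Replace the P < 0.1 gate with the following:
1. Name a short list of modifiers measured at baseline, before the first education visit, for EBF and timely initiation. Parity or previous breastfeeding and education are candidates. Leave out place and mode of delivery.
2. Settle the list before the 6-month data are analysed. Trial status says that month-one data are already collected and month-6 collection has begun, but the article plans no interim analysis and will analyse all outcomes after collection ends, so there is still time.
3. For every listed modifier, report the interaction estimate with its 95% CI and the effect in each subgroup, whatever the P-value.
4. State how many interactions were tested, and label all of them exploratory.

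A Holm or Bonferroni criterion may be added if the team wants to declare effect modification, but it is optional given the loss of power.

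The cost is a paragraph of text, one table or forest plot, and fewer modifiers examined. No further data or participants are needed.
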